### Randomization and blinding

The random sequence will be generated by the Center for Evidence-Based Medicine of Beijing University of Chinese Medicine using Statistical Analysis System (SAS version 9.2), and randomization will be stratified according to study center and DKD stage. Eligible patients with DKD of each stage will be randomized to the experimental group or the control group at a 1:1 ratio. The group numbers will be provided in envelopes made from carbonless paper. At each center, the envelopes will be kept by a study administrator who will not directly participate in the recruitment or follow-up of any participant, and the group numbers will be subsequently disclosed. The administrator will open one envelope and provide the participant with their group number on the day of inclusion.

Different people will serve as investigators, therapists, and assessors. Assessors of primary and secondary endpoints and data analysts will be blinded to the treatment allocation throughout the course of the study, while patients, investigators, and therapists administering the treatment will not be blinded.

### Intervention

Participants with DKD of each stage will receive basic treatment and TCM or basic treatment only for 24 consecutive weeks according to the random assignment.

#### Control group

Participants in the control group will receive basic treatment for DKD based on the recommendations of Treatment of Diabetic Kidney Disease 2014 by the Chinese Diabetes Society, including blood glucose control (HbA1c will be maintained below 8% throughout the trial), blood pressure control (participants with hypertension will receive antihypertensive drugs to maintain their blood pressure ≤ 130/80 mmHg, except for individuals aged 60 years or older, for whom the systolic pressure threshold will be ≤ 150 mmHg.

#### Experimental group

In addition to the above-mentioned basic treatment, participants in the experimental group will receive an oral traditional Chinese formula based on the *Zhenjia* theory, which is different for different stages of DKD. The *Tourexiaozhen* formula for participants with early stage DKD will consist of *Radix scutellariae* (*Huang Qin*), *Fructus forsythiae* (*Lian Qiao*), *Fructus arctii* (*Niu Bang Zi*), and *Radix scrophulariae* (*Xuan Shen*); the *Huoxuexiaozhen* formula for those with middle-stage DKD will include *Fructus arctii* (*Niu Bang Zi*), *Abelmoschus corolla* (*Huang Shu Kui Hua*), *Sargassum* (*Hai Zao*), *Hirudo* (*Shui Zhi*), and *Radix astragali* (*Huang Qi*); and the *Xiezhuoxiaozhen* formula for end-stage DKD will include *Radix astragali* (*Huang Qi*), *Cortex eucommiae* (*Du Zhong*), *Eupolyphaga seu steleophaga* (*Tu Bie Chong*), *Sargassum* (*Hai Zao*), *Radix et rhizoma rhe* (*Da Huang*), and *Rhizoma smilacis glabrae* (*Tu Fu Ling*). The ingredients in each formula can be adjusted individually at every visit according to patient’s signs and symptoms, and the dose of each ingredient in the prescription will be decided by the physician. The standard adjustments will be as follows: for patients with dry mouth or thirst, *Radix puerariae* (*Ge Gen*) will be added to the formula; for patients with bitter taste, *Radix bupleuri* (*Chai Hu*), *Radix scutellariae* (*Huang Qin*), and *Fructus aurantii immaturus* (*Zhi Shi*) will be added to the formula; for patients with low back pain, *Radix cyathulae* (*Chuan Niu Xi*), *Dipsaci radix* (*Xu Duan*), and *Rhizoma cibotii* (*Gou Ji*) will be added to the formula; for patients with edema, *Polyporus* (*Zhu Ling*), *Poria* (*Fu Ling*), *Rhizoma alismatis* (*Ze Xie*), *Pericarpium arecae* (*Da Fu Pi*), and *Exocarpium benincasae* (*Dong Gua Pi*) will be added to the formula; for patients with abdominal distension, *Radix aucklandiae* (*Mu Xiang*), *Fructus amomi* (*Sha Ren*), *Citrus medica* (*Xiang Yuan*), and *Fructus citri sarcodactylis* (*Fo Shou*) will be added to the formula; and for patients with itching skin, *Fructus kochiae* (*Di Fu Zi*) will be added to the formula. All formulae will be prescribed by a physician licensed in Chinese medicine and with at least 8 years of clinical experience. The formulae will be prepared in the form of granules by Beijing Tcmages Pharmaceutical Co., Ltd. (Beijing, China), a company that has passed the Chinese Good Manufacturing Practice for Pharmaceutical Products certification. A single-day supply will be provided in two doses (pouches) to be taken orally one at a time (twice a day).

### Outcomes

#### Primary outcomes

For early stage DKD, the primary outcome will be UAER. For middle-and advanced-stage DKD, the primary outcomes will be 24-h UP and eGFR, respectively.

#### Secondary outcomes

Physicochemical indicators: HbA1c, eGFR, Scr for early and middle-stage DKD and HbA1c, Scr, and blood urea nitrogen (BUN) for advanced-stage DKDTCM syndrome integral score, which will be determined using the TCM Syndrome Integral ScalePatient quality of life evaluated using Short Form 36-item Health Survey (SF-36)Microinflammation indicators: C-reactive protein (CRP), interleukin-6 (IL-6), and tumor necrosis factor α (TNF-α) levels

#### Safety outcomes

Complete blood count (CBC), AST, ALT, alkaline phosphatase (ALP), glutamyl transpeptidase (GGT), and total bilirubin (TBIL) tests and electrocardiography will be performed at baseline and at every study visit. The proportion of patients demonstrating adverse drug reactions (ADRs) in the experimental group will be compared with that in the control group. ADRs will be defined as undesirable, unexpected symptoms, signs, or diseases that occur during the clinical trial and can be caused by the treatment.

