### Adverse event (AE) reporting

AEs will be defined as undesirable, unexpected symptoms, signs, or diseases regardless of whether related to the treatment. If any AE happens, the investigators will take proper measures (dose adjustment, drug withdrawal, or symptomatic treatment) to ensure safety of the participant and perform continuous follow-up until the patient’s condition returns to normal. The relationship between the AEs and the experimental treatment will be further evaluated. All AEs and their characteristics, including the manifestation, onset date and time, duration, cause, relationship with the experimental treatment, specific therapy, and outcome, will be recorded.

In case of a severe AE (SAE) that can result in death, disability, hospitalization, or prolonged hospitalization, in addition to the above-mentioned measures, the chief investigator will be notified immediately and a written report will be submitted to the Research Ethics Committee within 24 h.

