### Statistical analysis

Statistical analysis will be conducted at the Center for Evidence-Based Medicine of Beijing University of Chinese Medicine using Statistic Package for Social Science (SPSS, version 22.0, Beijing University of Chinese Medicine). Intention-to-treat and per protocol sets will be used to analyze the efficacy of TCHM. A safety analysis set will be used to evaluate the safety of the trial. Missing outcome variables will be estimated using the principle of the last observation carried forward, with the data from the last study follow-up used as the final results.

The independent-samples *t* test or Mann-Whitney test will be used for comparison of the trial primary outcomes between the two groups, including UAER in the early stage subgroup, 24-h UP in the middle-stage subgroup, and eGFR in the advanced-stage subgroup, which are all continuous variables with four measurements. Moreover, repeated measures analysis of variance will be attempted to further test the time effect and treatment cross-effect. With regard to the secondary outcomes, the independent-samples *t* test or Mann-Whitney test will be used to analyze continuous variables, and the chi-squared test will be used to analyze classified variables. With regard to safety outcomes, the incidence of AEs will be determined and a comparison between the two groups will be attempted. A stratified analysis of data according to DKD stage or center will be attempted in order to decrease bias. A *P* value < 0.05 will be considered to indicate a statistically significant difference.

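### AEs and ADRs are both limited to unexpected events, and the article names two different between-arm safety comparisons

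*Protocol article*

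**What the plan says.** All of this is in the protocol article.

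- **Safety outcomes**, comparison: "The proportion of patients demonstrating adverse drug reactions (ADRs) in the experimental group will be compared with that in the control group". Definition: "ADRs will be defined as undesirable, unexpected symptoms, signs, or diseases that occur during the clinical trial and can be caused by the treatment".
- **Adverse event (AE) reporting**, definition: "AEs will be defined as undesirable, unexpected symptoms, signs, or diseases regardless of whether related to the treatment". Causality: "The relationship between the AEs and the experimental treatment will be further evaluated". The same section lists the cause of the event and its relationship with the experimental treatment as separate recorded items. It describes SAEs as a severe kind of AE.
- **Statistical analysis**, comparison: "the incidence of AEs will be determined and a comparison between the two groups will be attempted".
- **Randomization and blinding**, roles kept blind: "Assessors of primary and secondary endpoints and data analysts will be blinded to the treatment allocation throughout the course of the study". The section then lists the roles that know the allocation: "while patients, investigators, and therapists administering the treatment will not be blinded". Safety assessors are in neither list, and no section says who judges causality.
- **Control group**: "Participants in the control group will receive basic treatment for DKD", which covers glucose and blood pressure control. There is no herbal formula and no placebo.

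Blood counts, liver tests and electrocardiography are planned at baseline and every visit, with no restriction by arm.

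**The concern.** There are two separate problems.

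The first is the count. Whether an event was foreseen normally matters for how it is reported, not for whether it is an adverse event at all. Here it is part of both definitions. A reaction that the prescribing physician anticipates would be neither an AE nor an ADR. SAEs are described as a kind of AE, so they inherit the same limit.

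The second is the comparison. ADRs are a causally attributed subset of AEs, so the two sections name different endpoints that could point in different directions. The ADR version also depends on attribution, and the only relatedness judgement described is against a treatment that one arm does not receive.

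The Discussion in the abstract says the trial will provide evidence on safety as well as effectiveness. At stake is whether the reported between-arm figures can carry that claim.

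**Working it through.** **No safety figure to reproduce.** The article states no AE or ADR rate and no safety power. The only figure used from it is the total of 266 at 1:1, so 266/2 = 133 per arm, pooled over stages and before dropout. All event rates below are assumptions.

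**Step 1: the definitions side by side.** The AE and ADR definitions share the same opening conditions (undesirable and unexpected) and differ only on causality. Statistical analysis uses AEs and gives no other definition. Its comparison is therefore free of the causality condition but still carries the expectedness condition. The article gives no list of expected reactions. The Experimental group section lets ingredients be adjusted at every visit and leaves doses to the physician, so what counts as expected would be judged case by case.

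**Step 2: size of the under-count.** Suppose true AE proportions are p1 = 20% and p2 = 10%, and a share u of events in both arms is dropped as expected. The observed proportions are p1(1 − u) and p2(1 − u). Two-sided 0.05 power, by normal approximation with n = 133 and p̄ the mean of the two observed proportions, is

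Φ{ [difference − 1.96 × √(2p̄(1 − p̄)/n)] / √([p1(1 − p1) + p2(1 − p2)]/n) }, with the observed proportions put in for p1 and p2.

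| u | Observed | Difference | Calculation | Power |
|---|---|---|---|---|
| 0 | 20% v 10% | 10 points | (0.100 − 1.96 × 0.04379)/0.04336 = 0.33 | 63% |
| 0.25 | 15% v 7.5% | 7.5 points | (0.075 − 1.96 × 0.03875)/0.03847 = −0.02 | 49% |
| 0.50 | 10% v 5% | 5 points | (0.050 − 1.96 × 0.03230)/0.03215 = −0.41 | 34% |

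This assumes equal dropping in both arms. If the dropped events were exactly the foreseeable reactions to the formula, and these made up the whole 10-point excess, the observed figures would be 10% v 10% and the signal would vanish.

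**Step 3: the ADR comparison.** The Safety outcomes definition refers to the treatment without saying which one. The AE reporting section judges relatedness to the experimental treatment. Two readings follow:

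- *Any study treatment counts.* Control ADRs are possible, since controls receive protocol-specified drug treatment, but the relatedness item is not framed to capture them.
- *Only the formula counts.* A control event cannot qualify, and the comparison is of some proportion against zero.

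The second reading, the extreme one, shows what could happen. With k events against 0 and 133 per arm, the uncorrected chi-squared statistic is 266k/(266 − k). It is 3.03 at k = 3 and 4.06 at k = 4, against a critical value of 3.84, so four attributed events against none suffice. Let the true AE rate be equal in both arms, and let a share of experimental-arm AEs be attributed to the formula. The chance of declaring a difference is then P(X ≥ 4) for X binomial(133, AE rate × share):

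| AE rate, both arms | Share attributed | ADR proportion | Chance of a false difference |
|---|---|---|---|
| 10% | 10% | 1% | 5% |
| 10% | 30% | 3% | 57% |
| 20% | 30% | 6% | 96% |
| 30% | 50% | 15% | over 99.9% |

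Exact binomial probabilities are used because the normal approximation is unreliable at counts this small. Fisher's test would need six events against none (P = 0.030) and would give lower chances at the low end.

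**The case against.** The strongest reply is that Statistical analysis already plans an all-causality AE comparison, so safety does not rest on attribution. Neither section claims to be the only comparison, and the two could be complementary. That stands against any claim that the trial compares only ADRs. It does not answer the expectedness limit, which the AE comparison inherits.

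A reader might infer that the control ADR rate is zero by construction. The article does not support that. Its ADR definition refers to the treatment in general, controls receive active basic treatment, and the cause of an event is recorded separately from its relationship with the formula. The term is ambiguous. It does not fix the rate at zero, so the second table above is conditional on one reading.

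A reader might also infer that unblinded staff assign causality. This is plausible, since investigators manage AEs and are not blinded, but no section names the person who decides. A condensed article may leave that to the full protocol.

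On the word *unexpected*, one can say that it is loose drafting and that, with no list of expected reactions, nobody will filter by it. That may prove true in practice. It is still the stated rule, it appears in both definitions, and sites collect events under it. The scheduled blood tests and electrocardiograms give some protection that does not depend on attribution, but they do not capture symptoms.

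**Conclusion.** The point holds in limited form. Both definitions as written exclude foreseeable reactions, and the all-cause comparison inherits that under-count. The two sections name different between-arm safety endpoints, and the ADR version may not measure the arms alike.

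The size cannot be fixed from the article. On the assumed 20% v 10% rates, losing a quarter to a half of events takes power from 63% to 49% or 34%. If control ADRs could not be counted at all, the chance of a false ADR difference would run from 5% to over 99.9% over the assumed range.

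A reader might infer that the plan systematically understates, or overstates, the formula's harm. Neither follows. The expectedness limit lowers counts, while one-sided attribution could raise the apparent excess on the formula, and unblinded raters could also under-attribute. The net direction is not determined.

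**What to change.** 1. Delete *unexpected* from the AE and ADR definitions. Apply this prospectively, and check the CRFs and source records of patients already enrolled for events left out as expected.
2. In both Safety outcomes and Statistical analysis, make the between-arm safety comparison the proportion of patients with any AE and the proportion with any SAE, regardless of causality.
3. Report ADRs descriptively, and state which treatment the relatedness judgement refers to.

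The cost is small: wording in three sections, plus the record check. Trial status says recruitment is under way, so some events omitted under the current definition may not be recoverable. The change is better made soon.

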#### Laboratory tests

Routine laboratory tests (CBC and general urine analysis, Scr, BUN, AST, ALT, ALP, GGT, UAER, 24-h UP, and HbA1c) will be performed by the clinical laboratory of each center. For CRP, IL-6, and TNF-a level determination, an additional 3–5 mL of venous blood will be collected. The serum will be separated by centrifugation for 15 min at 3000×g, aliquoted, labeled concisely, and stored at − 80 °C until the final analysis. Repeated freeze-thaw cycles will be avoided. The inflammation indicators will be measured at the Research Center, Dongzhimen Hospital Affiliated to Beijing University of Chinese Medicine using specific ELISA kits.

### Adverse event (AE) reporting

AEs will be defined as undesirable, unexpected symptoms, signs, or diseases regardless of whether related to the treatment. If any AE happens, the investigators will take proper measures (dose adjustment, drug withdrawal, or symptomatic treatment) to ensure safety of the participant and perform continuous follow-up until the patient’s condition returns to normal. The relationship between the AEs and the experimental treatment will be further evaluated. All AEs and their characteristics, including the manifestation, onset date and time, duration, cause, relationship with the experimental treatment, specific therapy, and outcome, will be recorded.

In case of a severe AE (SAE) that can result in death, disability, hospitalization, or prolonged hospitalization, in addition to the above-mentioned measures, the chief investigator will be notified immediately and a written report will be submitted to the Research Ethics Committee within 24 h.

### Data collection

A standardized CRF designed for this study will be used to collect relevant data. The participants will be evaluated at baseline and weeks 4, 12, and 24. Each visit will have to occur within 5 days from the scheduled time. Information about the participants, including demographics, medical history, and previous medications, will be collected at baseline. Data on symptoms and TCM syndrome and results of physical examination and laboratory tests will be collected at each visit; HbA1c will be measured at baseline and at weeks 12 and 24. SF-36 will be administered only at the first and last visits. The schedule of the trial can be found in Fig. 2.

**Fig. 2 Fig2:**
[figure not shown]
Standard Protocol Items: Recommendations for Interventional Trials (SPIRIT) Figure. Laboratory examination includes complete blood count (CBC) and general urine analysis, potassium, calcium, phosphates, fasting blood glucose, liver function tests (AST, ALT, ALP, GGT, TBIL), renal; function (BUN, Scr), and serum lipids (cholesterol, triglycerides, and low-density lipoprotein levels), UAER for patients with early stage DKD, and 24-h UP and HbA1c for weeks 0, 12, and 24

### Quality assurance and data management

To ensure the quality of the study and its adherence to the protocol, physicians responsible for prescribing the experimental formula will be trained beforehand, whereas all investigators involved in the study will be trained in recruiting participants and will be provided a written protocol and a standardized record form.

All information from CRFs will be carefully recorded. Clinically unacceptable data will require investigation and explanation by the researcher. All errors will need to be corrected by crossing out, with the researcher’s signature and date. Withdrawals or/and missed follow-up visits will need to be explained in CRFs. After one participant completes the study at each center, the trial monitor will visit the site. The monitor will review the CRFs, check the inclusion, exclusion, and withdraw criteria, and compare the data in the CRFs to those in the source medical records. Any inadequacies or errors will be reviewed by the local investigator and coordinator.

Data from CRFs will ultimately be input into an electronic database (Epidata 3.1) designed for the trial. Data will be entered twice (independently by different persons). After the independent double entry, data will be checked by the database software. All non-identical items will be checked against the source medical records and corrected. Additionally, 10 CRFs will be randomly selected and compared manually with corresponding database entries. All study-related data and documentation will be retained at the Institute for Nephrology Research of Beijing University of Chinese Medicine. All personal information of potential and enrolled participants will be maintained to protect confidentiality before, during, and after the trial.

### Sample size

To estimate the group size, a small-scale study was conducted to measure the effects of TCHM in 90 patients, with 30 patients with DKD of each stage. Half of the patients regularly received herbal therapy, while the other half received basic treatment only. After 24 weeks, UAER in the control and experimental groups (early stage DKD) was70 ± 51 mg and 44 ± 27 mg, respectively, 24-h UP in the control and experimental groups (middle-stage DKD) was 3.25 ± 1.09 and 2.50 ± 0.95 g, respectively, and eGFR in the control and experimental groups (advanced-stage DKD) was 33.4 ± 9.1 and 40.5 ± 10.2 mL/min/1.73m^2^, respectively. Using early stage DKD as an example, the following formula was employed to calculate the sample size that would allow obtaining a significantly lower UAER in the experiment group after 24 weeks of treatment:$$ n={\left({\mu}_{\upalpha}+{\mu}_{\upbeta}\right)}^2\times \left(1+1/\mathrm{k}\right)\times {\sigma}^2/{\left({\mu}_2-{\mu}_1\right)}^2, $$

where *σ*^2^is overall variance, which was estimated as sample variance s^2^:$$ {s}^2=\left({s_1}^2+\mathrm{k}{s_2}^2\right)/\left(1+\mathrm{k}\right). $$

The proportion of cases between the experimental and control groups was set to 1:1(k = 1). The study was designed to have a power of approximately 90% and a one-side level of significance of 0.05 (*α* = 0.05, *β* = 0.1). *μ*_1_, *μ*_2_, *s*1, and *s*_2_ are mean and standard deviations in the control and experimental groups. This resulted in *n* = (1.64 + 1.28)^2^ × (51^2^ + 27^2^/(70 − 44)^2^ = 42.

Thus, after assuming a dropout rate of 20%, the sample size for the early stage subgroup in each group was determined to be 53. Similar calculations resulted in a sample size of 40 patients for the middle-stage and advanced-stage subgroups in each group. This produced the final sample size of 266 patients.

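### The 90% power rests on a one-sided 0.05 test, but the analysis section sets a non-directional P < 0.05; if that is two-sided, power at the planned evaluable numbers is about 82–84% per stage

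*Protocol article*

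**What the plan says.** In the protocol article, the Sample size section fixes the design level: "The study was designed to have a power of approximately 90% and a one-side level of significance of 0.05". The worked example uses 1.64 and 1.28, the normal quantiles for one-sided 5% and 90% power. The aim there is directional: a lower UAER in the experimental group at 24 weeks. The early-stage result is 42 per arm, raised to 53 for 20% dropout. Similar calculations give 40 per arm for the middle and advanced stages, and 266 in total.

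The Statistical analysis section plans, for the primary outcome of each stage, that the independent-samples t "test or Mann-Whitney test will be used for comparison of the trial primary outcomes between the two groups". It adds repeated measures analysis of variance for the time and treatment effects, and chi-squared tests for categorical secondary variables. One decision rule covers all of them: a P "value < 0.05 will be considered to indicate a statistically significant difference". The section mentions neither a one-sided nor a two-sided test. It plans intention-to-treat and per-protocol sets, with missing outcomes filled by last observation carried forward (LOCF).

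**The concern.** The design level and the decision rule do not match as written. A threshold of 0.05 for a difference, applied alike to t, Mann-Whitney, chi-squared and ANOVA tests, is ordinarily understood as two-sided. The sample size was not calculated for that test.

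Two things are at stake. First, if the tests are two-sided, the 90% power is overstated for all three primary comparisons. Second, while sidedness is not fixed in the analysis section, a favourable result with a two-sided P between 0.05 and 0.10 could be reported as positive by appeal to the Sample size section, or as negative by appeal to the usual reading of the Statistical analysis section. That choice should not remain open once results by arm can be seen.

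**Working it through.** **Inputs, all from the Sample size section.** Control and experimental values at 24 weeks:
- Early stage, UAER: 70 (SD 51) and 44 (SD 27) mg; difference 26.
- Middle stage, 24-h UP: "3.25 ± 1.09 and 2.50 ± 0.95 g, respectively"; difference 0.75.
- Advanced stage, eGFR: "33.4 ± 9.1 and 40.5 ± 10.2 mL/min/1.73m^2^, respectively"; difference 7.1.
- Allocation: "The proportion of cases between the experimental and control groups was set to 1:1(k = 1").
- Dropout: 20%.

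**Step 1: reproduce the plan.** With k = 1 the formula is n = (z_α + z_β)² × (s1² + s2²) / (difference)², and (1.64 + 1.28)² = 8.5264.
- Early: 8.5264 × (2601 + 729) / 676 = 42.0; 42 / 0.8 = 52.5, so 53.
- Middle: 8.5264 × (1.1881 + 0.9025) / 0.5625 = 31.7, so 32; 32 / 0.8 = 40.
- Advanced: 8.5264 × (82.81 + 104.04) / 50.41 = 31.6, so 32; 32 / 0.8 = 40.
- Total: 2 × (53 + 40 + 40) = 266.

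Every figure reproduces, and only with the one-sided quantile. (A closing bracket is missing from the printed early-stage formula; this is typographical and changes nothing.)

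**Step 2: power at the planned evaluable numbers.** With pooled SD s = √((s1² + s2²)/2), the signal is δ = difference / (s × √(2/n)). Normal-approximation power is Φ(δ − 1.645) one-sided and Φ(δ − 1.960) two-sided. The t figures use the noncentral t distribution with 2n − 2 degrees of freedom.

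| Stage | n per arm | δ | One-sided 0.05, normal / t | Two-sided 0.05, normal / t |
|---|---|---|---|---|
| Early | 42 | 2.920 | 89.9% / 89.5% | 83.2% / 82.3% |
| Middle | 32 | 2.934 | 90.1% / 89.6% | 83.5% / 82.3% |
| Advanced | 32 | 2.938 | 90.2% / 89.6% | 83.6% / 82.5% |

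Under a two-sided t test the type II error is therefore about 17.5% to 17.7%, against the planned 10%.

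**Step 3: every randomised patient counted in full.** With 53, 40 and 40 per arm and the full effect in all of them, δ is 3.280, 3.281 and 3.285. Two-sided power is then 90.7% in each stage by the normal formula, or 90.1%, 90.0% and 90.1% by t.

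**Step 4: dilution under LOCF.** The documents do not say how much of the 24-week effect a carried-forward value would show, so this is an assumption, with the SD held constant. If the 20% carried forward show half the effect, the mean difference is multiplied by 0.8 + 0.2 × 0.5 = 0.9, and two-sided power by t is about 83%. If they show none, the multiplier is 0.8 and power is about 74%.

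**Step 5: size of the gap in patients.** For 90% power at two-sided 0.05, the plan's formula with 1.960 and 1.282 gives 51.8, 39.1 and 38.9, so 52, 40 and 39 evaluable per arm. After 20% dropout this is 65, 50 and 49, or 2 × (65 + 50 + 49) = 328 in total against 266. This shows the scale only; it is not a proposal to enrol more.

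**The case against.** The strongest reply is that the contradiction is inferred. The Sample size section openly declares "a one-side level of significance of 0.05" and a directional aim, and the Statistical analysis section never says two-sided. If the declared level governs the primary tests, about 90% power stands. The chi-squared tests, which help the two-sided reading, apply only to secondary variables. The article is also condensed, and a fuller document may settle the matter. Much of this stands: a reader might infer that the trial will certainly be tested two-sided, and the documents do not support that certainty. What remains is that the section giving the decision rule does not carry over the level on which the sample size depends, and its wording points the other way.

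A second reply is that 82% describes completers only. The intention-to-treat analysis with LOCF keeps 53, 40 and 40 per arm, where nominal two-sided power is about 90%. This also stands as arithmetic, so 82% should not be presented as the trial's true power. It does not rescue the stated figure, because it needs carried-forward values to show the full 24-week effect, and the plan itself inflated for dropout because it did not count those patients. The per-protocol set gains nothing from it.

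A reader might also infer that adjusting for baseline would restore the lost power. That depends on the correlation between baseline and week 24, which the document does not give, so it cannot be relied on here.

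Finally, one-sided 0.05 is a declared choice and not in itself an error. That is fair; the objection is to leaving it out of the decision rule.

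**Conclusion.** The point holds in conditional form. The sidedness of the primary tests is not fixed in the Statistical analysis section and does not match the basis of the sample size.

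- If the tests are two-sided at 0.05, the stated 90% is about 6 to 8 percentage points too high at the planned evaluable numbers (82.3% to 83.6% across stages and methods). About 90% is reached only with all randomised patients counted and no dilution.
- If the tests are one-sided at 0.05, the power is as stated, and each stage carries a 5% false-positive rate for claiming benefit that the Statistical analysis section does not disclose.

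These figures assume that the pilot means and SDs are correct, that dropout is 20% in each arm, and that a t test is used. The shortfall affects the stated power and the decision rule, not the effect estimates. It should be corrected because all three primary conclusions depend on that rule.

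**What to change.** Before any comparison by arm is made or the analysts are unblinded, state the same sidedness in the Sample size and Statistical analysis sections. Two-sided 0.05 for all primary tests is preferable. The Sample size section should then say that the numbers were derived at one-sided 0.05, and that two-sided power at the planned evaluable 42, 32 and 32 per arm is about 82–84% per stage.

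If one-sided 0.05 is kept, the Statistical analysis section should say so for the primary tests, name the direction for each outcome (lower UAER, lower 24-h UP, higher eGFR), and disclose the 5% one-sided false-positive rate per stage.

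Recruitment is under way, and no change in enrolment is proposed. The cost is a short statement in each of two sections and, under the two-sided choice, a less favourable stated power.
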